### Randomisation

After receiving signed informed consent, 1:1:1:1 computerised (Castor Electronic Data Capture (Castor EDC)) randomisation will take place to each of the four groups. An authorised researcher will be able to perform randomisation and have insight in the randomisation results. Stratification will be applied based on the following variables: hormonal use (yes/no), diagnosis of irritable bowel syndrome (yes/no), baseline Eetscore-FFQ outcome (<100/100 to 130), and baseline pain NRS average score (4 to 6/7 to 10). Randomisation within each stratum will be conducted to ensure comparability across groups for these factors.

This study is single blinded. Participants, nutritionist, and psychologists cannot be blinded due to the nature of the interventions, the assessor is blinded for the treatment allocation. Breaking the randomisation code will be done when patient’s health is at risk or when investigation is required by the sponsor, the Medical Ethics Committee (METC) Oost-Nederland or the monitor.

### Variables

The primary outcome of this study is the pain intensity score, measured with NRS, to assess the most intense pain and the average pain during last month, and endometriosis-specific pain symptoms (eg, dyspareunia, dyschezia, gastrointestinal symptoms) on a 0–10 point scale.

Secondary outcome variables are considered to reflect potentially underlying mechanisms of the effect of both interventions on the primary outcome. We will investigate the influence of the AIDI, CBT, and the combination of both interventions on inflammatory markers and immune cell composition in PB and ME, the vaginal and gut microbiome, and hair cortisol levels. Furthermore, HRQoL will be assessed with the Endometriosis Health Profile-30 (EHP-30) and Short Form Healthy Survey-36 (SF-36).

Demographic variables will be recorded including age, height, weight, waist circumference, BMI, marital status, education level, occupation, the method used to diagnose endometriosis, year of diagnosis, type of endometriosis, use of contraception, use of analgesics, use of medication, presence of subfertility, parity, diet history, history of eating disorders, history of (self-reported) intestinal disorders, history of DSM-V diagnosis, and if patients underwent psychological treatment prior to inclusion in this study.

Additional outcome variables are pain anxiety which will be measured with the Pain Anxiety Symptom Scale (PASS), and pain catastrophising which will be measured by the Pain Catastrophising Scale (PCS). Moreover, sleep and physical activity level are assessed to minimise confounding factors. Therefore, participants will fill in the Pittsburgh Sleep Quality Index to assess sleep quality and the International Physical Activity Questionnaire Short Form to assess physical activity level. Additionally, fatigue is measured using the Checklist Individual Strength. Self-reported stress levels will be measured with the Perceived Stress Scale. The central sensitisation of pain is assessed using the Central Sensitisation Inventory. To assess the consistency of participants in adhering to their diet and to determine whether participation in the study prompts premature dietary changes, the Eetscore-FFQ will be administered three times throughout the intervention period. Patients’ experience following the AIDI and/or CBT will be measured with an evaluation questionnaire.

All primary, secondary, and additional variables will be measured at baseline (T0) and after the intervention period of 13 weeks (T2). Women with endometriosis will visit the hospital twice during the intervention period, at the start (T0) and end (T2) of the study. HC will not undergo any of the interventions and will have one hospital visit (T0). During the study visits PB will be drawn, scalp hair samples will be collected, and participants will hand in ME, a vaginal swab, and faecal sample.

Halfway through the study period (T1), for an interim measurement, women with endometriosis will fill in the Eetscore-FFQ, as part of an adherence measurement. In addition, they will be asked to complete the pain NRS and EHP-30.

To evaluate the long-term feasibility, cost-effectiveness and impact of the interventions, women with endometriosis will be asked to complete the pain NRS, EHP-30, and Eetscore-FFQ at 6 months after completing the study (T3).

### Sample collection and processing

#### Peripheral blood

PB is collected at T0 and T2. For plasma isolation, one 10 mL ethylene diamine tetra acetic acid (EDTA) tube (BD Vacutainer), and one 10 mL sodium heparin tube (BD Vacutainer) will be used. For the collection of serum isolation, one 4 mL serum tube (BD Vacutainer) will be used. Lastly, for peripheral mononuclear cell (PBMC) isolation, blood will be collected in two 10 mL EDTA tubes.

Tubes for serum and plasma collection will be centrifuged for 10 min at 20 °C 2204 rpm within 4 hours after collection. The collected samples will be stored in 1.4 mL round bottom tubes (Micronic) at −80 °C until further analysis.

PBMC will be isolated using the StraightFrom Whole Blood PBMC Isolation Kit (human, Miltenyi Biotec) according to the manufacturer protocol. In short, erythrocytes will be sedimented and removed using Sedimentation Buffer II with 5 mM EDTA in combination with Red Blood Cell removal antibodies from Sedimentation Kit II (human, Miltenyi Biotec). After centrifugation for 3 min at 20 °C 495 rpm, the supernatant will be collected and washed with MACS separation buffer. Granulocyte and erythrocyte will be depleted via magnetic separation. This will be done using Depletion MicroBeads and an autoMACS Separator. PBMCs will be frozen in RecoveryTM cell freezing medium (Gibco, Life Technologies) at a concentration of 10–20 × 10^6^ cells/mL, and will be stored at −80 °C for 24 hours before being transferred to liquid nitrogen until further analysis.

#### Menstrual effluent

Participants will be instructed to collect ME at home using a menstrual cup (AllMatters OrganiCup) at T0 and T2. The collection of ME starts after the initial spotting (ie, very light bleeding), and will be done for up to 30 hours. For the first and second 12 hours (total of 24 hours), the cup will be emptied in a collection tube containing RPMI1640 medium (ThermoFisher Scientific, Waltham, Massachusetts, USA) supplemented with 10% human pooled serum (HPS) (Zen-Bio, Durham, North Carolina, USA), 1 mM pyruvate (ThermoFisher Scientific), 2 mM GlutaMAX (ThermoFisher Scientific), 100 U/mL penicillin/100 µg/mL streptomycin (ThermoFisher Scientific), and 0.3% sodium citrate (Merck, Darmstadt, Germany). These samples will be stored at room temperature for a maximum of 48 hours until processing. A small fraction of the collected ME in the first 12 hours is separated in an empty 15 mL tube and will be stored at 4 °C until processing. The last 6 hours of the collected ME will be emptied in a 50 mL tube with RPMI1640 medium and stored at 4 °C until processing

To isolate menstrual mononuclear cells (MBMC), ME samples from the first 24 hours will be pooled and centrifuged for 5 min at 20 °C 1483 rpm. The medium will be removed and the pellet will be filtered using a 70 µm cell strainer (PluriSelect Life Science, Leipzig, Germany) by creating a vacuum using a connector ring (PluriSelect). A fraction of the filtered ME will be stored in PAXgene Blood RNA Tube (BD Bioscience) for transcriptomic analysis. The remaining ME will be 1:1 diluted in PBS+2% HPS. MBMC will be isolated according to the PBMC isolation procedure described above.

The other two tubes will be centrifuged for 10 min at 20 °C 2204 rpm. Supernatants from both tubes will be collected in 1.4 mL round bottom tubes and stored at −80 °C until further analysis of metabolites and epigenetic profiling of the liquid phase of the ME. The pellet of the 50 mL tube will be resuspended in 20% glycerol (Thermo Scientific Chemicals) and stored at −80 °C for epigenetic profiling of the solid phase of the ME.

#### Vaginal swab and faeces

Participants will be instructed to use the eNat vaginal swab (Copan Diagnostics) during the luteal phase of their menstrual cycle. Faeces will be collected in a faeces tube (76×20 mm, Sarstedt), maximum 24 hours prior to the study visit. Both samples will be stored at 4 °C until study visit. After the study visit, faeces and vaginal swab will be stored at −80 °C until DNA isolation using the DNeasy Blood & Tissue Kit (Qiagen) and subsequent microbiome analysis.

### Interventions

#### Standard care

The two primary components of standard care for endometriosis include the use of analgesics, like paracetamol or non-steroidal anti-inflammatory drugs or morphine. Moreover, another component is the use of hormonal therapies, such as oral contraceptives, progestogens or gonadotrophin‑releasing hormone analogues or antagonists. Standard care is individualised based on the participants’ needs and physicians’ choice.

#### Anti-inflammatory diet intervention

During the intervention period of 13 weeks, participants will receive a total of four consultations with a dietitian. One at T0, immediately prior to the start of the intervention, and three during the intervention period (beginning, middle (T1), and end (T2)). A 24h-recall will be done by the dietitian at T0, and three times during the AIDI. The information received from the 24h-recall at T0 will be used to create a personalised nutrition plan based on the AIDI, which will be further discussed during the in-person consultation at T0. Participants will furthermore receive a tailored dietary advice, along with an information folder containing recipes, food substitutions and two-week meal plans.

When a subject has questions or experiences issues concerning the dietary advice, she is allowed to request an extra phone consultation with the dietitian.

The AIDI that is used in this RCT is based on the Dutch Healthy Diet Index 2015 (DHD2015)^37^ and shares features with the EAT-Lancet, Mediterranean and Healthy Eating Index dietary patterns. It promotes a high intake of vegetables, fruits, legumes, nuts, fish, whole grains and dairy, while limiting red and processed meat, sugary drinks, salt, added sugars, and saturated fats.^38^ Compared with DHD2015, the AIDI is stricter regarding (red) meat intake, making it predominantly plant-based. Dietary guidelines are summarised in online supplemental table 1.

#### Cognitive behavioural therapy

For the CBT, a protocol has been developed in concordance with several psychologists having affinity with the treatment of women with endometriosis. This protocol is shown in online supplemental table 1. CBT will be provided by a trained psychologist with experience in the treatment of women with endometriosis. During the intervention period there will be in total seven individual CBT sessions. Psychologists will follow the protocol, but the treatment can be personalised based on the results of the PCS and PASS questionnaire. The first CBT session will take 1 hour and will take place face to face in the hospital, subsequent sessions will take approximately 45 min and may be done online.

In the first session, management of expectations towards the CBT (and AIDI) will be addressed. In the six other sessions, attention will be paid to the biological link between endometriosis-related pain and stress, relaxation training, cognitive stress management, sexual relationships, and the management of anxiety, catastrophising, and hypervigilance. When a participant is allocated to the SC + AIDI + CBT group, every CBT session will also focus on how to be able to adhere to the AIDI. In addition to the sessions provided by a psychologist, an online CBT module is available containing general information about psychological mechanisms of chronic pain and exercises on coping with pain in the context of behaviour, cognitions, and emotions. Participants in the SC + CBT and SC + AIDI + CBT group can use this online module freely to re-explore information already explained in the face-to-face sessions.

#### Data handling, storage and archiving

Data of participants will be handled confidentially and coded. The research data will be pseudo-anonymised by giving each participant a unique code. The code list, with both codes and names of the participants will only be accessible for the members of the research team and will be stored in a secured file. The handling of personal data will be done according to the General Data Protection Regulation. Data will be collected and stored in the cloud-based platform Castor EDC, and Labguru. Data and biological samples will be kept for 15 years to be able to perform additional analyses in case of new developments and insights. Participants can give their permission for this via the informed consent form.

### Statistical analysis

Data collected via questionnaires will be analysed using the software IBM SPSS V.29 for Microsoft Windows, data regarding the biological samples will be analysed using R software. The threshold for statistical significance is defined as <0.05.

For the primary outcome, pain NRS scores, repeated measures ANOVA will be conducted with time (T0 vs T2) as the within-participants variable, group (SC, SC + AIDI, SC + CBT, and SC + AIDI + CBT) as between-participant variable, and the pain NRS score as the dependent variable. If there are missing data, or a temporary study halt, a linear mixed model will be used instead of repeated measures ANOVA. Model fit will be assessed with residuals vs predicted plots and observed vs predicted plots. An intention-to-treat analysis will be followed in the case of follow-up losses. In this analysis, participants are analysed according to their original group assignment, regardless of whether they completed the treatment or dropped out, to minimise the risk of bias due to selective dropout. Given the random assignment of the intervention groups, a regression analysis on the pre-post change, adjusting for the pre-intervention score will be used to measure the main effect of the AIDI and CBT, and estimate interaction effects. Mediation analysis will be conducted to understand if and how secondary outcome measures mediate the effect of the intervention on the primary outcome.

To investigate the differences between women with and without endometriosis at baseline, a Welch’s ANOVA will be performed. This method is chosen to account for unequal group sizes and variances. In case the data are not normally distributed, a non-parametric Kruskal-Wallis test will be used.

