### Sample size calculation

The calculation of the required sample size for this RCT was conducted for the primary outcome, average pain intensity measured with a Numerical Rating Scale (NRS). Based on preliminary results of our single-arm explorative feasibility study and the RCT of Field *et al*, where a whole-food diet was implemented that restricts ultra-processed foods for pain management in chronic pain patients,^34^ we assume a pre-post correlation of r = 0.3. Although the single-arm trial found an effect (pre-post) of 1 SD, the expected effect size was set at 0.6 SD (–1.14).

For the CBT no pilot data were available. Therefore, the calculation of the effect size for this intervention was based on an RCT describing the efficacy of CBT in enhancing coping strategies, alleviating depression, stress, pain perception and improving the quality of life for women with endometriosis.^35^ In this study an effect of 0.55 SD was observed. For the current RCT this would translate to a similar effect of CBT as of the AIDI, so −1.14. We assume that the pre-post SD σ and correlation will be the same for all arms.

With 40 participants per arm, the precision for the main effects of AIDI and CBT yields an SD of 0.405, providing power greater than 80% for detecting an effect size of 1.14. However, the interaction effect has an SE of 0.57, ie, with a 95% CI for the estimated difference of ±1.12. This allows to observe an interaction effect in the order of magnitude of AIDI and CBT effects.

Based on our pilot-study we expect a dropout rate of 20–25%. Therefore, ten additional participants will be included in each arm of the RCT, resulting in a target sample size of 50 participants per arm, in total 200 women with endometriosis.

The evaluation of differences between HCs and women with endometriosis will be an explorative part of the study to generate preliminary insights. In the literature a sample size of 30–50 is described as a reasonable minimum sample size.^36^ Considering the potential drop-out and the group size in the other arms of the RCT, the total sample size for this RCT will be 250, of which 200 will be women diagnosed with endometriosis and 50 HC women.

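### Two unranked analyses of the primary outcome: the first-named repeated measures ANOVA is a change-score test with standard errors 24% larger, at r = 0.3, than those of the baseline-adjusted regression behind the sample size

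*Protocol article*

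**What the plan says.** The Statistical analysis section describes the analysis of the primary outcome in one paragraph with three elements.

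- First: "repeated measures ANOVA will be conducted with time (T0 vs T2) as the within-participants variable". The between-participant factor is group, with four levels (SC, SC + AIDI, SC + CBT, SC + AIDI + CBT).
- Second: a linear mixed model replaces this ANOVA if data are missing or the study is temporarily halted. Its fixed effects and its handling of baseline are not described.
- Third: "a regression analysis on the pre-post change, adjusting for the pre-intervention score will be used to measure the main effect". This model covers both factors and also their interaction.

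No sentence ranks these. The significance rule is general: "The threshold for statistical significance is defined as <0.05".

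The Sample size calculation section gives the planning inputs. For the diet, "the expected effect size was set at 0.6 SD", equated to 1.14 NRS points, and CBT is assumed to have a similar effect. On correlation, "we assume a pre-post correlation of r = 0.3". On variability, "We assume that the pre-post SD σ and correlation will be the same for all arms". The resulting precision is given as follows: "With 40 participants per arm, the precision for the main effects of AIDI and CBT yields an SD of 0.405". The power claim that rests on this figure is worded as "providing power greater than 80% for detecting an effect size of 1.14". For the interaction it states an SE of 0.57 and a 95% CI of ±1.12.

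**The concern.** With two measurement times, the group-by-time F test of a repeated measures ANOVA is the same test as a one-way ANOVA on the T2 minus T0 change. It makes no use of the pre-post correlation beyond plain subtraction. When that correlation is as low as 0.3, subtracting the baseline adds noise. Regression on the baseline removes it.

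Two things follow. The analysis introduced for the primary outcome is less precise than the one that the sample size figures describe. And a four-level group factor gives a 3-df omnibus test, whereas the trial is a 2 × 2 factorial sized for an AIDI effect, a CBT effect and their interaction. The omnibus test isolates none of these.

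At stake are the precision promised for the interaction and a clear confirmatory result. Two analyses of one outcome, with different hypotheses and standard errors and no ranking, leave room to choose after the results are known.

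**Working it through.** **Inputs (Sample size calculation).** Effect 1.14 = 0.6 SD, so SD = 1.14/0.6 = 1.9. r = 0.3. 40 analysed per arm. Two-sided 5% is assumed, because the article does not state sidedness; the interaction CI of ±1.12 on an SE of 0.57 implies a multiplier of 1.96. Equal SDs at T0 and T2 are also assumed. The text states a common SD and correlation across arms and does not explicitly say the same across times.

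**Step 1: residual SD under each analysis.**
- Baseline-adjusted: 1.9 × √(1 − 0.3²) = 1.9 × √0.91 = 1.812
- Change score: 1.9 × √(2(1 − 0.3)) = 1.9 × √1.40 = 2.248
- Ratio: 2.248/1.812 = √(2/(1 + r)) = √(2/1.3) = 1.240

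**Step 2: reproduce the plan's figures.** With the baseline-adjusted SD:
- 40 vs 40 contrast: 1.812 × √(2/40) = 0.405, as stated
- Interaction: 1.812 × √(4/40) = 0.573, as stated (0.57); CI half-width 1.96 × 0.573 = 1.12, as stated
- Power for 1.14: Φ(1.14/0.4053 − 1.96) = Φ(0.853) = 80.3%, as stated (above 80%)

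The alternatives do not give 0.405: change score 40 vs 40 gives 0.503, change score 80 vs 80 gives 0.355, T2 score alone 40 vs 40 gives 0.425, and baseline-adjusted 80 vs 80 gives 0.287. The planning figures therefore belong to the baseline-adjusted model.

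**Step 3: the same contrasts under each analysis, 40 per arm, effect 1.14.**

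| Contrast | Baseline-adjusted SE | Power | Change-score SE | Power |
|---|---|---|---|---|
| 40 vs 40 | 0.405 | 80% | 0.503 | 62% |
| Pooled main effect, 80 vs 80 | 0.287 | 98% | 0.355 | 89% |
| Interaction | 0.573 (CI ±1.12) | 51% | 0.711 (CI ±1.39) | 36% |

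Restoring 80% power for the 40 vs 40 contrast with change scores would take 62 per arm. The plan states no power for the interaction, so only its SE and CI can be set against a stated figure.

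**Step 4: the 3-df omnibus test** (non-central F with 3 and 156 df).
- Only one factor works: 76% power with change scores, 92% baseline-adjusted.
- All three active arms improve by 1.14 over SC: 62% and 83%.
- Effects are additive (0, 1.14, 1.14, 2.28): 98% and above 99%.

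**Step 5: sensitivity of the 24%.**
- By correlation, √(2/(1 + r)): 35% at r = 0.1, 24% at 0.3, 15% at 0.5, 8% at 0.7.
- By unequal SDs: entry requires an NRS above 4, which could narrow the spread at T0. For illustration, assume SD 1.3 at T0, 1.9 at T2 and r = 0.3. The change SD is √(1.69 + 3.61 − 1.48) = 1.95, and 1.95/1.81 is an inflation of about 8%.

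**The case against.** Four arguments on the other side carry weight.

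1. **The matching model is already in the plan.** The regression on change, adjusted for the pre-intervention score, is the model that reproduces the sample size, and the text assigns the factorial effects to it. One can read the ANOVA as an overall test and the regression as the estimation step. This stands: the plan does contain an analysis that answers the factorial question. What is missing is the statement that it is primary, and the ANOVA is the analysis introduced for the primary outcome.

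2. **The stated power survives for pooled main effects.** The sample size section attaches 0.405 and 80% to the main effects. Pooled over the other factor, a change-score analysis gives SE 0.355 and 89% power, better than both figures. This stands. The fall to 62% concerns the 40 vs 40 contrast that numerically yields 0.405. That this figure is called the precision of the main effects is a separate labelling matter.

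3. **The ANOVA will probably not be run.** With 20–25% dropout expected, the mixed model will almost certainly replace it. This stands, but it does not settle the point. If baseline means are left free by group, the mixed model's group-by-time contrast is close to the change-score analysis. If they are constrained equal, it is close to the baseline-adjusted one. A full protocol or SAP may say which, so its absence from the article is not itself the criticism.

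4. **The 24% is conditional.** It needs r = 0.3 and equal SDs at both times. This stands, and the range is given above; r = 0.3 is nevertheless the plan's own value.

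A reader might infer that the trial has only 62% power, or that its primary analysis is invalid. The documents support neither. The 62% belongs to one contrast under one of the two analyses, and under randomisation a change-score comparison is unbiased. The issue is efficiency and an unstated hierarchy.

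**Conclusion.** The point holds in a limited form. The article names two analyses for the same outcome without ranking them. The first-named one, a 3-df change-score test, does not itself estimate the AIDI, CBT and interaction effects, and it is less efficient than the model on which the trial was sized. The clearest conflict with a stated figure is the interaction, where the change-score SE and CI exceed the planned ones by 24%. Main effects pooled over the other factor remain adequately powered under either analysis. The size rests on SD 1.9, r = 0.3, 40 analysed per arm, a two-sided 5% level and equal SDs at T0 and T2. A higher correlation or a narrower T0 spread would shrink the loss to roughly 8–15%, but the lack of a ranking would remain.

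**What to change.** Name one primary analysis: the regression already in the Statistical analysis section, with T2 average pain NRS (or its change from T0) regressed on AIDI, CBT, AIDI × CBT and the T0 NRS score. Label the repeated measures ANOVA as supportive, or drop it. State that the mixed model used when data are missing has the same factorial terms, with T0 either as a covariate or as a baseline mean common to all groups, and not an unconstrained four-group-by-time structure.

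The cost is a few sentences in the protocol or SAP. Sample size, data collection and visits do not change. Recruitment is planned to run to the end of 2026, so the change can be made and dated before outcome data are analysed.

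### The AIDI, CBT and interaction effects come from a T0–T2 change regression that omits women without T2 pain, and the T1 pain score that could protect against selective dropout is named in no analysis

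*Protocol article*

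**What the plan says.** All references are to the protocol article.

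- **Variables.** Pain NRS is measured at T0 and T2. Of the halfway visit (T1) the article says: "In addition, they will be asked to complete the pain NRS and EHP-30".
- **Statistical analysis, first model.** A repeated measures ANOVA of pain NRS, with time defined as T0 versus T2 and the four arms as the group factor.
- **Statistical analysis, missing data.** "If there are missing data, or a temporary study halt, a linear mixed model will be used instead of repeated measures ANOVA". The time points of the mixed model are not restated.
- **Statistical analysis, dropout.** "An intention-to-treat analysis will be followed in the case of follow-up losses". This is explained as analysis by assigned arm whether or not the woman completed treatment or dropped out, with the stated aim of limiting bias from selective dropout.
- **Statistical analysis, factorial effects.** The AIDI and CBT main effects and their interaction come from "a regression analysis on the pre-post change, adjusting for the pre-intervention score".
- **Sample size calculation.** Dropout of 20–25% is expected. Each arm is raised from 40 to 50, giving 200 women.

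**The concern.** A woman without T2 has no change score, so the regression that yields the treatment effects is a complete-case analysis on T2. The missing-data clause does not cover it, because that clause substitutes a mixed model for the ANOVA only. With 20–25% dropout expected, the switch to the mixed model is close to certain. If that model inherits T0 and T2, a woman without T2 adds only a pre-treatment score, which says nothing about her response.

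Both models then need dropout to depend on nothing beyond baseline pain and group. That is a strong assumption here. Participants are not blinded, and the active arms involve four dietitian consultations, seven CBT sessions, or both. A woman's pain halfway through could well influence whether she stays. The trial records that pain score but has no stated use for it in the analysis. At stake is a biased treatment effect, in either direction, that data already being collected could largely prevent under this kind of dropout.

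**Working it through.** **1. The plan's own figures.** An effect of 1.14 points equal to 0.6 SD gives SD = 1.14/0.6 = 1.9. With the stated pre-post correlation ("we assume a pre-post correlation of r = 0.3"), the baseline-adjusted residual SD is 1.9 × √(1 − 0.3²) = 1.812.

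- SE for 40 versus 40: 1.812 × √(2/40) = 0.405, as stated. Power is 80.3% (stated: above 80%).
- Interaction SE: 1.812 × √(4/40) = 0.573 (stated 0.57), with CI half-width 1.96 × 0.573 = 1.12, as stated.

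The planned precision thus belongs to a baseline-adjusted analysis of women with T2.

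**2. How many women are affected.** 0.20 × 200 = 40 and 0.25 × 200 = 50 women without T2. The change regression omits them all.

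**3. Bias.** The documents give no dropout mechanism, no dropout timing and no correlation involving T1, so these are assumed.

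*Simulation A:* 2,000 trials per scenario, 50 per arm, SD 1.9, corr(T0,T2) 0.3, corr(T0,T1) 0.4, corr(T1,T2) 0.5–0.7, T1 effect 70% of the T2 effect, about 20% lost, 60% of losses after T1, and dropout in the active arms only related to T1 pain (log-odds 0.7–1.2 per SD). The true simple effect is −1.14.

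- Baseline-adjusted complete cases: −1.199, −1.240, −1.245, −1.291.
- Using T1: −1.139, −1.153, −1.146, −1.142.
- Bias without T1: 1.199 − 1.14 = 0.06 to 1.291 − 1.14 = 0.15 points, or 5–13%. Against the planned SE this is 0.06/0.405 = 15% to 0.15/0.405 = 37% of one SE.

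*Simulation B:* large sample, two arms, 22.5% lost, all after T1, corr(T0,T1) = corr(T1,T2) = 0.3 / 0.5 / 0.7.

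| Dropout related to T1 pain | Change regression | Mixed model, T0 and T2 | Mixed model, T0, T1 and T2 |
|---|---|---|---|
| Alike in both arms | −1.145 / −1.134 / −1.143 | −1.144 / −1.136 / −1.142 | −1.144 / −1.136 / −1.142 |
| Active arm only | −1.211 / −1.276 / −1.321 | −1.210 / −1.276 / −1.312 | −1.131 / −1.146 / −1.126 |
| Opposite directions | −1.295 / −1.400 / −1.522 | −1.295 / −1.395 / −1.519 | −1.141 / −1.133 / −1.139 |

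A mixed model on T0 and T2 gives practically the same answer as the change regression. Only the addition of T1 changes it.

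**4. From simple to factorial effects.** Suppose each of the three active arms carries bias b and SC carries none. The AIDI main effect averages (AIDI − SC) and (AIDI + CBT − CBT), so its bias is [(b − 0) + (b − b)]/2 = b/2. With b of 0.06–0.15 that is about 0.03–0.08 points. The interaction bias is (b − b) − (b − 0) = −b, the same size as the simple-effect bias and opposite in sign, so the combination looks less than additive.

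**5. Precision.** The variance of the T2 mean is proportional to (1 − p²)/n₂ + p²/n₁, where p is the partial T1–T2 correlation given T0, n₂ women have T2 and n₁ have T1. With T1 correlations of 0.5, p = (0.5 − 0.5 × 0.3)/√(0.75 × 0.91) = 0.424. At 20% dropout with half the losses after T1, n₂ = 40 and n₁ = 45. The effective n is 40.8 per arm, a 2.0% reduction in variance. Over T1 correlations of 0.3–0.7, 25–100% of losses after T1 and 20–25% dropout, the reduction runs from 0.3% to 12.9%.

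**The case against.** A reader might infer that the intention-to-treat claim fails for the whole analysis. The documents do not support that. The article defines intention-to-treat as analysis by assigned arm. A likelihood-based mixed model, even on T0 and T2 only, keeps every woman with a baseline score in her arm and is valid if dropout depends on baseline pain and group. Leaving out T1 makes that assumption more demanding; it does not breach the definition. Women who stop treatment but complete T2 are analysed in every model. The conflict with the promise is confined to the change regression.

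A reader might also infer that the plan rules T1 out. It does not: the mixed model's time points are simply not restated, and the full protocol or a statistical analysis plan may add T1. T0 and T2 is the natural reading, no more. The article itself, however, fixes the ANOVA's time factor, names the change regression as the source of the factorial effects, and states the aim about dropout. The tension between these is therefore on the page.

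Finally, a reader might infer that the plan overstates the benefit. That holds only under the assumed mechanism. The simulations generate dropout from T1 pain, so a model containing T1 is bound to recover the truth. If dropout works alike across arms the bias is almost nil, and high-pain women leaving SC could offset or reverse it. Baseline-adjusted change is also a standard endpoint analysis. These points limit the size of the concern. They do not explain why the protection the article promises is absent from the model that yields the effects.

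**Conclusion.** The point holds in limited form. The regression that gives the AIDI, CBT and interaction effects is complete-case on T2 and leaves out the 40–50 women expected to lack it, contrary to the stated aim for dropouts. The mixed-model fallback replaces only the ANOVA and, read naturally, does not use T1.

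The consequence is conditional. If dropout after T1 depends on T1 pain in the active arms only, a true simple effect of −1.14 is estimated at about −1.2 to −1.3. Opposite mechanisms in the two arms give up to −1.52 in the most extreme case tried. These sizes rest on assumed timing, mechanism and T1 correlations. The case for change rests on bias, not on precision. It is worth correcting before analysis, though it does not threaten the trial.

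**What to change.** Pre-specify one primary model and use it from the start, so that there is no switch when data turn out to be missing:

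- a likelihood-based linear mixed model for average pain at T0, T1 and T2, with unstructured covariance;
- AIDI, CBT, AIDI × CBT and their interactions with visit;
- baseline means constrained equal across arms, so that every randomised woman with any pain score is kept. Using T0 as a covariate is an alternative, but it leaves out women with neither T1 nor T2. If 60% of losses come after T1, that is 0.40 × 40 = 16 to 0.40 × 50 = 20 women;
- the T2 contrasts as the primary estimates of the main and interaction effects.

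Make the change regression a sensitivity analysis, and state the missing-at-random assumption in words: dropout may depend on arm and on pain already recorded at T0 and T1.

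The cost is new wording and slightly more analysis work. T1 pain is already collected, and inclusion is planned to run to the end of 2026. The model still does not deal with dropout driven by unrecorded pain after T1, or with losses before T1 that depend on unrecorded pain.
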